#### Longitudinal and short-term risk analysis

Repeated measurements of physiological and biomarker variables will be analyzed using linear mixed-effects models with random intercepts and random slopes when supported by the data. Time will be modeled as follow-up visit or continuous time since enrolment. Short-term risk will be evaluated using extended Cox models with time-varying covariates. Biomarker and physiological measurements will be updated at each follow-up visit and incorporated as time-dependent variables. For participants with incident AMI, measurements will be aligned relative to the event time. Predefined time windows preceding AMI will be constructed, and values within these windows will be analyzed. Within-individual changes will be defined as differences between consecutive measurements or relative to baseline values. Associations between time-updated variables and AMI risk will be estimated using time-varying Cox models.

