Baseline assessment: The project will be carried out from 2025 to 2027 in Gansu Provincial People’s Hospital, Aksay County People’s Hospital, Linxia Prefecture People’s Hospital, Gannan Tibetan Autonomous Prefecture People’s Hospital, and Dingxi City People’s Hospital. High-risk cardiovascular patients of the Han, Hui, Tibetan, and Kazakh ethnic groups will be identified through cardiovascular outpatient clinics, community screening programs, and electronic medical record systems. Follow-Up: it will be conducted at 3, 6, 9, 12, 15, 18, 21, and 24 months after enrollment in the cohort, for a period of 2 years. *Standardized assessment: Demographics, lifestyle, psychology, diet, and medication adherence questionnaires. +Sociodemographic characteristics: Age, sex, ethnicity, residence type, education, occupation, and income. ++Lifestyle factors: Smoking, alcohol consumption, dietary habits, physical activity, and sleep quality. †Clinical history: Hypertension, diabetes, dyslipidemia, previous stroke or TIA, family history of coronary heart disease, and history of drug use. ‡Anthropometry and physiological parameters: Including height, weight, BMI, waist circumference, blood pressure and body fat percentage. **Fasting venous blood tests: High-sensitivity C-reactive protein (hs-CRP), high-sensitivity troponin I (hs-TnI), creatine kinase (CK), creatine kinase-MB (CK-MB), lactate dehydrogenase (LDH), aspartate aminotransferase (AST), soluble suppression of tumorigenicity 2 (sST2), N-terminal pro–B-type natriuretic peptide (NT-proBNP), lipoprotein-associated phospholipase A2 (Lp-PLA2), fasting glucose, insulin, hemoglobin A1c (HbA1c), and a full lipid panel (total cholesterol, low-density lipoprotein cholesterol(LDL-C), high-density lipoprotein cholesterol (HDL-C), and triglycerides. ¶72-h wearable electrocardiogram (ECG) monitoring: A validated clinical-grade device (Shanghai Yishi Technology Co., Ltd.) will be used to continuously conduct 72-h wearable ECG and heart rate variability (HRV) monitoring. The data will be transmitted in real-time to a secure cloud platform, and the NARON CardioAI system will be used for automatic analysis, waveform classification, and feature extractio. ¶¶Transthoracic echocardiography: Unless there are other clinical indications, an echocardiogram will be performed once a year to evaluate the left ventricular ejection fraction and the situation of abnormal wall motion. ***Coronary computed tomography angiography (CCTA): If there are clinical indications should be repeated every 12 months. Assessment Tools: Includes the Rose Angina Questionnaire, The Canadian Cardiovascular Society Angina Classification, The Patient Health Questionnaire-9 (PHQ-9), The Generalized Anxiety Disorder-7 (GAD-7), The Perceived Stress Scale - 10 (PSS-10), The Pittsburgh Sleep Quality Index (PSQI), The Semi-quantitative Food Frequency Questionnaire (FFQ), The International Physical Activity Questionnaire Short Form (IPAQ-SF), The General Medication Adherence Scale (GMAS).

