#### Nested case–control component

Within the cohort, participants who develop incident AMI will be defined as cases, and matched controls will be selected from the risk set. Stored biospecimens from these participants will be used to assess variation in circulating biomarkers as short-term risk indicators prior to AMI, supporting analysis of temporal changes in risk within the cohort.

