### Outcomes

The primary outcome is first incident AMI during the 24-month follow-up period. AMI events will be adjudicated according to the Fourth Universal Definition of Myocardial Infarction (2018), based on cardiac biomarker changes together with clinical, electrocardiographic, imaging, and symptom-related evidence. This outcome is defined to capture short-term occurrence of major cardiovascular events within individuals, allowing assessment of variation in near-term risk across populations with different environmental exposures, ethnic backgrounds, and healthcare accessibility.

Secondary outcomes include longitudinal changes in physiological and biochemical indicators, healthcare utilization, and short-term variation in risk markers preceding AMI. Repeated measurements of biomarkers and physiological parameters will be used to evaluate temporal changes within individuals, particularly within the 90 days preceding AMI, to characterize short-term fluctuations in cardiovascular risk. In addition, differences in these trajectories will be examined across environmental and ethnic subgroups to assess population-level heterogeneity in risk patterns.

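### Cardiac injury markers serve both as AMI evidence and as time-updated predictors, with no stated minimum sample-to-event interval and no definition of event time, so a visit sample from an evolving AMI could count as a pre-AMI predictor

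*Protocol article*

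**What the plan says.** - **Predictor side.** The notes to Table 1 list "high-sensitivity troponin I (hs-TnI), creatine kinase (CK), creatine kinase-MB (CK-MB), lactate dehydrogenase (LDH" and AST in the fasting blood panel. Table 1 marks that panel at baseline and at all eight follow-up visits. Under Longitudinal and short-term risk analysis, "Biomarker and physiological measurements will be updated at each follow-up visit and incorporated as time-dependent variables", with no exception for injury markers. Risk prediction analysis makes repeated biomarkers candidate predictors. The Nested case–control component uses stored samples to "assess variation in circulating biomarkers as short-term risk indicators prior to AMI".
- **Outcome side.** Under Outcomes, AMI is adjudicated "based on cardiac biomarker changes together with clinical, electrocardiographic, imaging, and symptom-related evidence". No individual marker is named.
- **Timing.** "For participants with incident AMI, measurements will be aligned relative to the event time", and "Predefined time windows preceding AMI will be constructed, and values within these windows will be analyzed". The only window given a length is in Outcomes: "particularly within the 90 days preceding AMI". Event time is not tied to symptom onset, presentation or diagnosis, and no lag is stated.
- **Safeguards.** Acute illness is an exclusion at enrolment only. The adjudication panel is independent and blinded, but what it is blinded to is not stated.

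**The concern.** A marker that rises because an infarction has begun is part of the event, not a forerunner of it. Suppose a participant comes to the month-9 visit with chest discomfort since the evening before, the scheduled draw shows a high hs-TnI, and AMI is confirmed the next day. If the event is dated at diagnosis, nothing in the printed rule stops that value from being the covariate that explains the event. It could equally fall in the 90-day window or be used as a case sample in the nested set. Blinding the panel does not cure this, because the problem lies in the predictor value and its date.

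The study's question is whether change shortly before a first AMI carries information. Leakage of this kind would raise hazard ratios and the C-statistic for the markers most likely to be reported as early signals, and would present detection of an infarction as prediction of one.

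**Working it through.** **Number of events.** The article expects about 80. Directly, 2,340 × 0.04 = 93.6. With a loss of 14.5%, 2,340 × 0.855 × 0.04 = 80.0. No loss rate is printed and the calculation is placed in Supplementary Material 1, so 80 is used here only to set the scale.

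**How often a scheduled visit falls just before diagnosis.** Visits are about 91.3 days apart. If visit dates are independent of onset, the share of events with a visit in the last w days is w/91.3:
- w = 1: 1.1%, or 0.9 of 80
- w = 3: 3.3%, or 2.6 of 80
- w = 7: 7.7%, or 6.1 of 80

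This is a minimum if visits help to detect events. Each visit includes the Rose questionnaire, angina grading, a symptom update and hs-TnI, so some AMIs may be found because of the visit.

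**Effect on a marker with no true association (log scale).** Assumptions not in the documents: SD of ln(hs-TnI) 0.8 and a 20- to 50-fold rise in a contaminated sample. The shift is ln(20)/0.8 = 3.74 SD or ln(50)/0.8 = 4.89 SD. With k contaminated samples among 80 cases, the case mean moves by k × shift/80, which approximates the log hazard ratio per SD. Its standard error is about √(1/80 + 1/2,260) = 0.114.
- k = 1: 0.047 to 0.061, HR about 1.05 to 1.06; rejection about 7 to 8%
- k = 3: 0.140 to 0.183, HR about 1.15 to 1.20; 0.140/0.114 = 1.23 and 0.183/0.114 = 1.61 standard errors, so rejection about 23 to 36%

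Null simulations with 80 cases and 2,260 non-cases agree: HR 1.05 to 1.07 for k = 1, and about 1.14 to 1.19 with 22 to 34% rejection for k = 3. With k = 0, rejection is about 4%.

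**Risk-set Cox simulation** (between-person SD 0.8, within-person SD 0.3, 60 runs per setting), HR per SD for a 5-fold / 20-fold rise:
- 1.1% of events contaminated: 1.01 / 1.05
- 3.3%: 1.03 / 1.10
- 7.7%: 1.17 / 1.30 (rejection 27% / 60%)
- 20%, an assumed case in which visits trigger detection: 1.45 / 2.00 (87% / 100%)
- 20% and 20-fold, with a lag that removes the contaminated samples: 1.01, rejection 5%

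**Other scales.** Primary outcome analysis keeps continuous variables on their original scale. If that carries over to the time-varying models, one contaminated sample gives about 38 to 45% false rejection. The plan also analyses differences between consecutive measurements, where between-person spread cancels. With three contaminated samples, the HR per SD of change is 1.14 (5-fold, 20% rejection) or 1.27 (20-fold, 67%).

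**The case against.** The strongest reply has four parts.

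1. *Contamination is conditional.* Covariates are updated at follow-up visits, and windows and nested samples must precede AMI. A reader might infer that blood taken at the AMI admission enters the models. No section says so. A visit must fall inside an unrecognised infarction, and the event must be dated after that sample. This stands, and it is why the point is worded as a possibility.

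2. *The article does not say which markers define AMI, where the windows end, or which nested sample is used.* A reader might infer that CK and CK-MB are defining evidence, that windows run right up to the event, or that the last stored sample is taken. The inference is reasonable for hs-TnI, less certain for CK and CK-MB, and the other two are not stated.

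3. *An article condenses a fuller document.* The windows are called predefined, so their limits may be set elsewhere. This stands for the limits. It does not dispose of the updating rule, which is printed and covers all biomarkers without exception. The Discussion concedes that visits may miss rapid fluctuations, but does not mention overlap between predictor and outcome.

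4. *The effect is small by chance alone.* For the one-day example this is right on the log scale. The larger figures need several contaminated samples, and the documents give no contamination rate. Treating every sample in the last seven days as raised 20- to 50-fold would overstate the matter, since a sample taken five to seven days before diagnosis is not shown to come from the infarction.

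A lag also sets aside some genuine late change, which the study wants to see. That is a reason to report both lagged and unlagged results.

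**Conclusion.** The concern holds in a limited form. The printed rule lets a visit sample from an evolving AMI act as a predictor of that AMI, because event time is undefined and no sample-to-event interval is set for markers that overlap with the outcome evidence. It does not show that such samples will be counted.

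Chance coincidence implies roughly 1 to 3 of 80 events, and more if visits lead to detection. On the log scale the bias is small for one sample and material for three. It is larger on the original scale or for change scores. These sizes rest on assumed variances and fold-rises, and on visit timing independent of onset.

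A reader might infer that the primary hazard ratios are biased as well. The article does not support that: the primary Cox model uses baseline variables, and acute illness at enrolment is excluded. The concern is confined to the time-varying, pre-AMI window, prediction and nested case–control analyses. It is an inexpensive improvement that does not undermine the design.

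**What to change.** In Longitudinal and short-term risk analysis, Risk prediction analysis, and the nested case–control text:

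1. For all biomarker analyses, date AMI at symptom onset, or at first objective evidence if silent, and use only samples drawn before that date.
2. Prespecify a lag for the cardiac injury markers, for example 7 days, with an unlagged sensitivity analysis. Apply the same lag to risk-set controls relative to the matched case's event date. The length is a design choice.
3. Report short-term associations and prediction performance with and without hs-TnI, CK, CK-MB, LDH and AST, and after excluding AMIs first detected at a scheduled visit.
4. State whether the adjudication panel sees the study-visit biomarkers.

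This takes a few sentences and no new data. With a 7-day lag, about 6 of 80 cases (80 × 7/91.3) would have their last sample replaced by the previous one. That sample lies a further 91 days or so back, so these cases would have no value left in the 90-day window. Some real late change is set aside in the lagged analysis, and hazard ratios may be less favourable. Settling this before events accrue avoids a later choice that could move the main short-term result.

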#### Additional analyses

Within the nested case–control component, conditional logistic regression models will be used to assess associations between biomarker indicators and AMI risk. Exploratory analyses using machine learning methods will be conducted to assess nonlinear relationships and interactions. Sensitivity analyses will be performed to evaluate the robustness of findings. Missing data will be addressed using multiple imputation.

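### The event-aligned windows before AMI are built for cases only and are not linked to the planned risk-set controls, so for physiological and ECG measures they mix pre-AMI change with drift over follow-up

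*Protocol article*

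**What the plan says.** All references are to the Protocol article.

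- **Outcomes** lists short-term variation in risk markers before AMI as a secondary outcome. It concerns biomarkers and physiological parameters, with emphasis on the last 90 days, and the trajectories are to be compared across environmental and ethnic subgroups.
- **Longitudinal and short-term risk analysis** says how: "For participants with incident AMI, measurements will be aligned relative to the event time". It continues: "Predefined time windows preceding AMI will be constructed, and values within these windows will be analyzed". Change is then defined: "Within-individual changes will be defined as differences between consecutive measurements or relative to baseline values".
- The same section also plans "Associations between time-updated variables and AMI risk will be estimated using time-varying Cox models". Its mixed models use a different time axis: "Time will be modeled as follow-up visit or continuous time since enrolment".
- **Nested case–control component** provides event-free comparators: "participants who develop incident AMI will be defined as cases, and matched controls will be selected from the risk set". Their stated use is "Stored biospecimens from these participants will be used to assess variation in circulating biomarkers as short-term risk indicators prior to AMI". **Additional analyses** keeps to that scope: "conditional logistic regression models will be used to assess associations between biomarker indicators and AMI risk".
- **Table 1** schedules physiological measures and blood tests at every three-monthly visit, and wearable ECG every six months, for all participants.

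**The concern.** Counting back from the event, windows further from it lie on average earlier in follow-up. A curve drawn from cases alone therefore shows two things at once: change that heralds AMI, and change that anyone in the cohort would show with time since enrolment. Drift of the second kind is plausible here, because participants are selected for high estimated risk and selected high values tend to settle on remeasurement.

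For circulating biomarkers the risk-set controls offer a reference. For blood pressure, heart rate, body measures and ECG or HRV, the text gives the windows none. The study could then present cohort-wide drift as a pre-infarction pattern, or miss a real rise masked by a general fall. In the subgroup comparison, drift that differs between sites would look like ethnic or environmental heterogeneity, which is the question the Introduction sets for the study.

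**Working it through.** **1. Number of cases.** Study population gives 2,340 participants, 4% incidence over 24 months and about 80 events. Directly, 2,340 × 0.04 = 93.6. The figure of 80 corresponds to 80/0.04 = 2,000 participants, that is 1 − 2,000/2,340 = 14.5% attrition. The article states no attrition rate and its supplement is not shown. I use the article's own 80; 94 cases would make the case-only results below slightly worse.

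**2. What a case-only window estimates.** Write the mean change in cases as δ + θ, where δ is drift common to the cohort and θ is change specific to impending AMI. Cases alone estimate δ + θ. Controls still at risk at the same time since enrolment estimate δ, so the difference estimates θ. Between groups g and h, case-only curves differ by (δg − δh) + (θg − θh), so unequal drift alone produces a difference.

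**3. Size when θ = 0.** The drift d, as a fraction of the SD of change, is not in the documents and is assumed over a range. For a two-sided 5% test with n = 80, the rejection rate is Φ(d√n − 1.96) + Φ(−d√n − 1.96), with √80 = 8.94.

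| Assumed drift d | d√80 | Case-only, formula | Case-only, simulated | Four time-matched controls per case, simulated |
|---|---|---|---|---|
| 0 | 0 | 5.0% | 5.4% | 5.1% |
| 0.1 | 0.89 | 14.5% | 14.5% | 5.3% |
| 0.2 | 1.79 | 43.2% | 42.3% | 4.7% |
| 0.3 | 2.68 | 76.5% | 75.8% | 4.8% |

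The simulation used 20,000 runs and normal changes with equal SD in cases and controls.

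**4. Does it matter when the drift occurs?** The table assumes that the measured change carries the whole drift. Suppose instead that all drift falls between baseline and month 3, and events are uniform over 24 months. Cases with two prior values have their event after month 3: 80 × 21/24 = 70. The last consecutive difference carries the drift only for events in months 3 to 6, which is 3/21 = 1/7 of them. At d = 0.3 the mean shift in standard errors is 0.3 × √70 / 7 = 0.36, and the rejection rate is about 6.5%. Change from baseline keeps all of it: 0.3 × √70 = 2.51, and the rejection rate is about 71%. The article allows either definition of change.

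**5. Price of adding controls.** With m independent controls per case and equal SD, the standard error is multiplied by √(1 + 1/m). For m = 4 this is 1.118 (+12%), for m = 2 it is 1.225 (+22%), and for m = 1 it is 1.414 (+41%). The article gives no ratio.

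**The case against.** The strongest reply is that the main short-term analysis already has a comparator. The extended Cox models use biomarker and physiological values updated at each visit, and the Abstract says such models will relate within-individual change to AMI. Follow-up time runs from enrolment (Primary outcome analysis), so each case is set against everyone still at risk at the same point, and common drift largely cancels in the hazard ratio. This stands. A reader might infer that the study has no means of telling pre-AMI change from drift; the Cox models, and the risk-set controls for biomarkers, show that this goes too far.

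Further points also stand in part:

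- No case-only significance test is written down; the text says only that window values will be analysed. The rates above describe what such a test would do.
- Drift confined to the first months does little to consecutive differences, as step 4 shows.
- One might extend the point to sleep, stress or activity questionnaires. The window text and the 90-day outcome name biomarkers and physiological parameters, so that extension is not supported.
- Risk-set sampling implies the case's event time as the control's index date, and the supplement or an analysis plan may carry the details.

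What remains is what the article itself fixes. It restricts event-time alignment to participants with AMI and restricts the nested component to biomarkers. The Cox model gives an association; it does not give the trajectories before the event that Outcomes intends to compare between groups. The mixed models run on visit or time since enrolment, with no term stated that separates cases from others.

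**Conclusion.** The point holds for the event-aligned window analysis, not for the study as a whole. For physiological measures, and for ECG and HRV, which the Discussion counts among physiological indicators, the windows have no stated comparator. Taken alone they confound pre-AMI change with drift over follow-up. Their comparison across ethnic or environmental groups is open to site-specific drift.

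The size is conditional: about 14% to 76% false rejection for assumed drift of 0.1 to 0.3 SD of change with 80 cases, against about 5% with time-matched controls. Early drift matters mainly for change from baseline. The direction of the bias does not depend on the assumed control ratio. It affects a secondary outcome and can be repaired cheaply with measurements already scheduled, so it is worth changing before analysis.

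**What to change.** - Give each risk-set control the index date of its case, at the same time since enrolment. Matching on calendar quarter as well is optional and shrinks the control pool somewhat.
- Build the same predefined windows for cases and controls, for all repeatedly measured physiological and ECG variables as well as biomarkers.
- Use the case-minus-control difference in change for the secondary outcome, and compare that difference across ethnic and environmental groups. Site-specific drift cancels only if controls come from the case's own centre or group, so the matching should say so.
- Label case-only curves as descriptive.
- Keep the time-varying Cox models as planned, and state that they run on time since enrolment.

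The cost is wording and some programming; the controls are already planned and Table 1 already schedules their measurements. Intervals widen modestly, by about 12% with four controls per case and more with fewer.

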### Study population

A total of approximately 2,340 adults will be enrolled from five participating centers, representing Han, Hui, Tibetan, and Kazakh populations across regions with varying altitude, environmental exposure, and healthcare accessibility. Recruitment targets are prespecified according to catchment characteristics, with planned enrolment of 900–1,050 Han, 650–750 Hui, 400–500 Tibetan, and 250–350 Kazakh participants. Sample size estimation is based on an event-driven approach (Supplementary Material 1). Assuming a 4% cumulative incidence of first AMI over 24 months, approximately 80 events are expected, supporting multivariable modeling and subgroup analyses.

Participants will be eligible if they: (1) are aged 30–85 years; (2) have an estimated 10-year atherosclerotic cardiovascular disease (ASCVD) risk ≥20% (6); (3) are permanent residents of the study area (≥6 months per year); (4) provide written informed consent; and (5) agree to repeated follow-up and biospecimen collection. Exclusion criteria include: (1) major comorbid conditions such as end-stage renal disease, hepatic failure, or active malignancy; (2) acute illness at enrolment; (3) severe psychiatric disorders; (4) substance abuse; and (5) pregnancy or breastfeeding (17). Loss to follow-up is defined as absence from more than two scheduled visits or permanent discontinuation. Follow-up will be maintained through clinic visits supplemented by telephone or electronic contact where necessary.

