### Variables and data collection

#### Baseline variables

At enrolment, participants undergo standardized assessments including questionnaires, physical examination, laboratory testing, cardiovascular imaging, and physiological monitoring (Table 1; Figure 2). These measurements are designed to capture both individual-level risk factors and population-level variation related to environmental and ethnic contexts. Sociodemographic variables include age, sex, ethnicity, residence type (urban or rural), education level, occupation, and household income. Clinical history captures physician-diagnosed hypertension, diabetes mellitus, dyslipidaemia, prior stroke or transient ischemic attack (TIA), and family history of coronary artery disease (CAD), together with current medication use. Lifestyle-related variables include smoking status, classified as never, former, or current smoking, alcohol consumption, dietary patterns, physical activity level, sleep quality, medication adherence, and psychological status, which may vary across environmental and sociocultural settings. Physiological measurements include systolic blood pressure, diastolic blood pressure, resting heart rate, body mass index, waist circumference, and body fat percentage (18). Laboratory biomarkers include inflammatory and cardiac stress markers, cardiac enzymes, and metabolic indicators reflecting glucose and lipid metabolism (Supplementary material) (13, 19, 20). Cardiac imaging includes transthoracic echocardiography and coronary computed tomography angiography (CCTA) where clinically indicated. Continuous 72-h electrocardiogram (ECG) and heart rate variability (HRV) monitoring are performed at baseline using a clinically validated wearable device (ref) (Supplementary material). Data are collected using standardized procedures and processed according to predefined quality-control criteria to ensure comparability across study sites.

**Table 1 tab1:** Schedule of assessments and data collection in the AMI cohort study.

Evaluation parameters	Baseline	Follow-up							
		3 m	6 m	9 m	12 m	15 m	18 m	21 m	24 m
Informed consent	x								
Inclusion criteria met	x								
Standardized assessment*	x								
Sociodemographic characteristics+	x								
Lifestyle factors++	x								
Clinical history†	x								
Anthropometry and physiological parameters‡	x	x	x	x	x	x	x	x	x
Fasting venous blood test**	x	x	x	x	x	x	x	x	x
72-h wearable electrocardiogram monitoring¶	x		x		x		x		x

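### Entry on a high baseline risk estimate, with change then measured from baseline, lets regression to the mean into the first 3-month step for score-related markers

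*Protocol article*

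**What the plan says.** Under Study population, a participant must "have an estimated 10-year atherosclerotic cardiovascular disease (ASCVD) risk ≥20"%. In Table 1 the row "Inclusion criteria met" is ticked in the baseline column only. Blood pressure and the fasting lipid panel are first measured in that same column, and no screening or run-in visit is listed. The notes to Table 1 add that high-risk patients "will be identified through cardiovascular outpatient clinics, community screening programs, and electronic medical record systems". The article does not say whether the values that qualify a person are the baseline values or earlier ones.

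Under Longitudinal and short-term risk analysis, change is defined in two alternative ways: "Within-individual changes will be defined as differences between consecutive measurements or relative to baseline values". For the mixed models, "Time will be modeled as follow-up visit or continuous time since enrolment". Under Outcomes, "differences in these trajectories will be examined across environmental and ethnic subgroups to assess population-level heterogeneity in risk patterns". Regression to the mean is not mentioned in the analysis sections or among the limitations in the Discussion.

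**The concern.** A threshold on a score built partly from error-prone readings over-selects people whose readings happened to be high that day. At the next visit those readings move back towards the person's usual level. If the same readings serve as the reference for change, the return is recorded as within-person improvement.

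Within-person change and its variation across populations are the study's stated aims, so an artefact here falls on the target of the research. The size of the return depends on how far the threshold lies above a group's own average and on how reliable the readings are. Groups or sites that differ in either would show different falls with no real difference in trajectory.

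**Working it through.** **The plan's own figure.** The only design figure that bears on this point is the expected event count, about 80. 2,340 × 4% = 93.6, whereas 80 / 0.04 = 2,000 people, which is 85.5% of 2,340. That fits about 14.5% attrition. The rate is not in the article and the calculation is referred to Supplementary Material 1, so no error is claimed. The count is used below only to cost the fix.

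**Inputs from the article.** Risk threshold of 20%; visits every 3 months to 24 months (baseline plus 8); "planned enrolment of 900–1,050 Han, 650–750 Hui, 400–500 Tibetan, and 250–350 Kazakh participants", with midpoints 975 Han, 450 Tibetan and 300 Kazakh.

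**Assumed inputs (not in the article).** Systolic pressure SD 18 mmHg; correlation *a* of the marker with the score; visit-to-visit reliability *ρ*; eligible fraction *p* of the source population; independent deviations from visit to visit; no true change.

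**Spurious fall.** Fall = SD × *a* × (1 − *ρ*) × *λ*, where *λ* = φ(k)/*p* is the mean of a standard normal variable above the cut-off k. *λ* is 2.06, 1.75, 1.40 and 1.16 for *p* = 5%, 10%, 20% and 30%.

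- Low: 18 × 0.2 × 0.2 × 1.16 = 0.8 mmHg (*p* = 30%).
- Central: 18 × 0.5 × 0.3 × 1.75 = 4.7 mmHg (*p* = 10%; *a* = 0.5 means the marker carries 25% of the score variance).
- High: 18 × 0.6 × 0.5 × 1.75 = 9.5 mmHg (*p* = 10%).

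A second grid (score share 10% to 50%, *ρ* 0.6 to 0.8, *p* 5% to 30%) gives 1.3 to 10.5 mmHg.

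**Where it appears.** In simulation with no true change, every change from baseline carried the fall. Only the first consecutive difference did; the later ones were about 0.00 SD. For a straight line through nine equally spaced visits with only baseline raised, the fitted slope is −(4/60) × fall per visit, so −0.533 × fall over the 8 intervals. A fall of 4.7 mmHg becomes a spurious 2.5 mmHg decline over 24 months. A slope fitted to months 3 to 24 was about 0.00 SD in every scenario.

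**Differences between groups.** Suppose two groups differ in source risk by 0.7 SD, so that 10% and 28% are eligible. The spurious difference in change was then 0.025 to 0.165 SD (× 18 = 0.5 to 3.0 mmHg). A two-sided 5% test would declare it in 11% to 85% of studies for 975 versus 450, and in 9% to 74% for 975 versus 300. With equal eligible fraction, reliability and score–marker relation, the difference is 0 and the error rate stays at 5%.

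A more extreme pairing, 5% versus 30% eligible at *a* = 0.5 and *ρ* = 0.7, gives 5.6 − 3.1 = 2.4 mmHg (from unrounded values). The SD of change is 18 × √(2 × 0.3) ≈ 14, so SE = 14 × √(1/975 + 1/300) = 0.92 and z ≈ 2.6. This sets the two ends of an assumed range against each other and is not a typical case.

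**Cox models.** The mean shift is largely shared by cases and those still at risk. The simulated correlation between a person's stable level and change from baseline was 0.01 to 0.12, and about 0 for later consecutive differences.

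**The case against.** Five points can be made for the plan.

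- **The qualifying readings may not be the baseline readings.** This stands as a limit. Candidates are also found through screening and records, and where earlier values qualify them, part of the regression is over before baseline. It does not remove the problem. If sites differ in which readings they use, the artefact differs by site, and the Study design section shows that site and predominant ethnicity largely coincide.
- **The analysis already allows for it.** Partly true. Consecutive differences are affected only in the first interval, and time as visit, if categorical, would isolate that step. But change from baseline and continuous time are equally permitted, and nothing says which contrasts carry the subgroup comparison.
- **Much of the panel is barely touched.** True. Markers such as sST2 and Lp-PLA2, and the questionnaire scores, would be affected only weakly. The point concerns blood pressure, lipids and their correlates.
- **This belongs in an analysis plan.** Knots and adjustments often do. The definition of change, however, is fixed in the article, and it is the definition that admits the artefact.
- **Trajectories are secondary.** True. The primary Cox analysis uses baseline values and is unaffected.

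A reader might go further and infer that false ethnic differences must follow, or that the AMI hazard ratios are seriously biased. The documents support neither. The first needs unequal selection or reliability. That is plausible, since the Introduction and Discussion describe distinct cardiometabolic profiles, but no eligible fractions are given. The second would mainly concern a model with change as the only term, which the article does not specify. It would arise chiefly from the correlation between change and starting level, not from selection.

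**Conclusion.** The concern holds in a limited form. If followed as written, the plan can report a fall of roughly 1 to 10 mmHg in systolic pressure (about 5 in a central case) between baseline and 3 months where nothing has changed, with a corresponding artefact in other score-related markers. The figures rest on the assumed SD, reliability, score correlation and eligible fraction, and on qualifying readings being baseline readings, which Table 1 suggests but does not state. A false ethnic or site contrast is possible, not certain. The descriptive trajectories and subgroup slopes are what need protecting. The matter should be settled before analysis, but it does not threaten the primary outcome analysis.

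**What to change.** In Longitudinal and short-term risk analysis:

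1. In the mixed models for score-related markers, give the baseline-to-3-month step its own term (a knot at 3 months, or visit as a categorical factor). Interact it with ethnicity and the other subgroup factors, and base subgroup comparisons of trajectory on slopes from 3 months onward.
2. Wherever change from baseline or a consecutive difference enters a time-varying Cox model, include the starting level as well.
3. Record, by site, whether the qualifying readings are the baseline readings, and report a sensitivity analysis that leaves out the baseline-to-3-month interval.

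Do not move the reference to the 3-month visit in the Cox analyses. With a constant hazard, 80 × 3/24 = 10 events fall in each interval. The first 10 have no post-baseline value under either rule. A 3-month reference would also lose the 10 in months 3 to 6, leaving about 20 of 80 without a usable change.

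The cost is wording and one recorded item, with no new visits or samples. Slopes become slightly less precise, and genuine change in the first 3 months is reported separately and not read as a group difference in trajectory.
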